**Fig. 1 Fig1:**
[figure not shown]
SPIRIT Flow Diagram for Tanzania: PPIUD study quantitative data collection by hospital group

**Fig. 2 Fig2:**
[figure not shown]
SPIRIT Flow Diagram for Nepal and Sri Lanka: PPIUD study quantitative data collection by hospital group

### Sample size

Following the cluster-randomized stepped-wedge design, power calculations were performed on a per country basis, assuming that 300 women are enrolled per hospital per month over a 12-month study enrolment period in Tanzania and an 18-month study enrolment period in Nepal and Sri Lanka, and followed for up to 18 months postpartum to ascertain study endpoints [13]. It is expected that the study will enrol 21,600 women in Tanzania and 32,400 women in Nepal and Sri Lanka.PPIUD Counselling – Assuming that at the study hospitals during the standard of care time periods, the PPIUD counselling rate will be 1% or lower, we will have 80% power or more to detect an increased counselling rate of 2% or greater, even with an ICC of 15% [14] or lower, assuming that at least 21,600 women are enrolled during the 12-18-month enrolment period.PPIUD Uptake – Assuming that at the study hospitals during the standard of care time periods, the PPIUD uptake rate will be 1% or lower, we will have 80% power or more to detect an increased PPIUD uptake rate of 8% or higher, even with an ICC of 15% or lower.PPIUD Expulsion Rate at 6 weeks – Assuming that the PPIUD uptake rate increased to 8% during the intervention periods at the study hospitals, there will be 80% power or greater if the PPIUD expulsion rate is assumed to be 20% before the intervention [15] and drops to 5% or less after the intervention, for an ICC of 5% or less, even with 20% loss to follow-up postpartum or less. These analyses apply only to the intervention periods at the six hospitals, and are based upon a one-sample test for clustered data.Modern contraceptive use at 6 weeks and 18 months – Assuming that modern contraceptive use at 6 weeks will be 55% in Sri Lanka [16] and that it will increase to 62% due to the availability of PPIUD during the intervention periods, there will be 80% power or more to detect this difference or anything greater, even if 20% of the participants enrolled during the antenatal period are lost to follow-up by the six week postpartum milestone and if the ICC is 15% or less. In Tanzania and Nepal, power is greater due to significantly lower modern contraceptive use at 6 weeks in the control group. Scenarios are similar for modern contraceptive use at 18 months.Proportion pregnant within 18 months of index pregnancy – Assuming that 24% of women who enrol during the control periods are pregnant again within 18 months [17], there will be 80% power or more to detect a decreased proportion pregnant by 18 months of 19.4% or less, even if 20% of the clients enrolled during the antenatal period are lost to follow-up by 18 months and if the ICC is 15% or less.

Thus, we conservatively expect excellent power within each of the 3 countries for all primary endpoints of this study, assuming 21,600 in Tanzania and 32,400 women in Nepal and Sri Lanka are enrolled across the study hospitals at a rate of 300/month. If between-country heterogeneity analysis indicates that the effect sizes between the countries appear to be comparable, we will pool the results across the three countries for substantially greater power.

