### Randomization of hospitals

Because of the potential benefit of the intervention to all women, a cluster-randomized stepped wedge design was considered most appropriate for the study. Six hospitals were selected in each country to provide national geographic coverage, and were randomized into two groups of three. Facilities were matched by number of deliveries per year, and one was randomly selected from each pair to be assigned to Group 1 while the other was assigned to Group 2. Using Stata software, researchers at Harvard T.H. Chan School of Public Health generated a random number that was assigned to each hospital. The hospital with the higher random number in the pair was assigned to Group 2, while the hospital with the lower random number in the pair was assigned to Group 1. A full list of study facilities is available upon request. The study enrolment period for both groups will be 12 months in Tanzania and 18 months in Nepal and Sri Lanka. In Group 1, the baseline standard of care (SOC) period will be three months and the PPIUD intervention period will be nine months in Tanzania and fifteen months in Nepal and Sri Lanka. In Group 2, the baseline (SOC) period will be nine months and the PPIUD intervention period three months in Tanzania and nine months in Nepal and Sri Lanka. We can represent this design for each group as follows:

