### Participant selection criteria

#### Women

Selection criteria for the study vary by country based on local regulations and the structure of the health system. In Sri Lanka, women will be eligible to participate in the study (inclusion criterion) if they deliver in one of the six study hospitals during the 18-month enrolment period, unless they normally reside outside of Sri Lanka. The study will interview women at up to four time points: baseline (in the hospital soon after delivery), 4-8 weeks postpartum for those who have PPIUD inserted, 9 months postpartum, and 18 months postpartum. In Sri Lanka, primary care services such as child immunizations are not available in the study hospitals, and the 9-month and 18-month surveys will be completed in satellite clinics affiliated with the study hospitals. There can be many satellite clinics affiliated with each hospital, and three to four will be selected based on geographic representation and the percentage of women delivering in the study hospitals who may receive postnatal care at the selected satellite clinics. Women enrolled at baseline will be eligible to complete the 9-month and 18-month surveys if they live in the catchment for one of the selected satellite clinics.

In Nepal, women will be eligible to participate in the study if they deliver in one of the six study hospitals during the 18-month enrolment period, unless they normally reside outside of the country. As in Sri Lanka, the study will interview women at up to four time points: baseline (in the hospital soon after delivery), 4-8 weeks postpartum for those who have PPIUD inserted, 9 months postpartum, and 18 months postpartum. In Nepal, because of the mountainous terrain and long travel times to reach remote areas, only women who live within 24 h of the study hospital will be eligible for the 9-month and 18-month follow up. Due to the high delivery caseload in the six hospitals selected in Nepal, a 55% sample of women enrolled at baseline who live within 24 h of the study hospital will be randomly selected to complete the two long-term follow up interviews at 9 months and 18 months postpartum. The long-term follow-up interviews will be conducted in the hospital when possible, but for participants unable to return to the hospital, enumerators will conduct interviews at the participant’s home or another location of the participant’s choosing.

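### Power is stated for contraceptive use at 6 weeks, which is surveyed only in PPIUD acceptors, and the 18-month power removes only 20% of enrolled women although planned long-term follow-up is restricted

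*Protocol article*

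**What the plan says.** **Power statements (Protocol article, Sample size).** The calculation is per country, "assuming that 300 women are enrolled per hospital per month", and the expected totals are stated: "It is expected that the study will enrol 21,600 women in Tanzania and 32,400 women in Nepal and Sri Lanka". For contraceptive use the text reads "Assuming that modern contraceptive use at 6 weeks will be 55% in Sri Lanka", with a rise to 62% in the intervention periods, 80% power or more, 20% loss by six weeks and an ICC up to 15%. The 18-month scenario is said to be similar. For pregnancy, 24% against 19.4% is powered at 80% or more, "even if 20% of the clients enrolled during the antenatal period are lost to follow-up by 18 months". The section closes by expecting excellent power in every country on full enrolment.

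**Who is measured (Participant selection criteria, Women).** The early interview is at "4-8 weeks postpartum for those who have PPIUD inserted". Outcome measures and Data collection procedures (Quantitative) apply the same restriction. For the 9- and 18-month interviews:

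- Nepal takes "a 55% sample of women enrolled at baseline" from those living within 24 hours of the hospital.
- Sri Lanka admits women "if they live in the catchment for one of the selected satellite clinics", with three to four clinics selected.
- Tanzania recruits at selected satellite clinics, and selection does not depend on baseline enrolment.

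Baseline enrolment takes place on postnatal wards. The contraceptive-use outcomes described under Outcome measures are at 9 and 18 months.

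**The concern.** A power statement should describe an outcome that will be observed, in the women who will be observed. Here the 6-week contrast needs contraceptive status in women without a PPIUD, who are nearly all of the control periods, and no such data are planned at that time. The 18-month statements take 80% of everyone enrolled as measured, but the eligibility rules exclude many of those women before any loss occurs. At stake is whether the excellent power expected in each country rests on the trial as designed. The pregnancy endpoint matters most here because it has the smaller margin.

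**Working it through.** **1. Who has data at 6 weeks.** Group 1 has three months of standard of care ("In Group 1, the baseline standard of care (SOC) period will be three months") and Group 2 has nine. The intervention then runs 9 and 3 months in Tanzania, and 15 and 9 months in Nepal and Sri Lanka. There are three hospitals per group and 300 women per hospital-month.

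- Control, each country: (3 x 3 + 3 x 9) x 300 = 36 x 300 = 10,800 women; 1% uptake gives 108.
- Intervention, Tanzania: (3 x 9 + 3 x 3) x 300 = 36 x 300 = 10,800; 8% gives 864. Total surveyed 864 + 108 = 972 of 21,600 (4.5%).
- Intervention, Nepal or Sri Lanka: (3 x 15 + 3 x 9) x 300 = 72 x 300 = 21,600; 8% gives 1,728. Total surveyed 1,728 + 108 = 1,836 of 32,400 (5.7%).

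All of these women accepted a PPIUD, so 55% against 62% among all delivering women cannot be estimated from them.

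**2. Who has data at 18 months.** The assumed number in Nepal or Sri Lanka is 0.80 x 32,400 = 25,920. In Nepal the plan allows at most 0.55 x 32,400 = 17,820 selected, and 0.55 x 0.80 x 32,400 = 14,256 (44%) after the plan's own 20% loss. The 24-hour restriction lowers this further by an unstated amount. For Sri Lanka and Tanzania no number can be derived.

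**3. Model for power.** The article does not give its formula. I used the standard stepped-wedge weighted least-squares model:

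- Six hospitals, fixed period effects and a constant hospital effect. Periods are 3/6/9 months (Nepal, Sri Lanka) or 3/6/3 months (Tanzania).
- With p the mean of the two rates, total variance s = p(1 - p): 0.585 x 0.415 = 0.2428 for use and 0.217 x 0.783 = 0.1699 for pregnancy.
- Hospital-period means have variance s(1 - ICC)/n + s x ICC and covariance s x ICC, with n = 300 x months x fraction measured.
- Power = Phi(|difference|/SE - 1.96). Two-sided 5% is an assumption.

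**4. The plan's own scenario first (80% measured, ICC 15%).** Nepal/Sri Lanka: use, SE 0.01197, power 99.99%; pregnancy, SE 0.01001, 0.046/0.01001 - 1.96 = 2.64, power 99.6%. Tanzania: 99.9% and 97.8%. The stated floor of 80% is met. The plan's differences of 7 and 4.6 points are not recovered as 80% boundaries. Under this model the boundaries are about 3.4-3.9 points for use and 2.8-3.2 for pregnancy.

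**5. Nepal at its ceiling (44%).** Pregnancy, ICC 15%: SE 0.01350, 0.046/0.01350 - 1.96 = 1.45, power 92.6%. With ICC 1%: SE 0.01443, power 89.0%. Use: 99.1% (ICC 15%) and 98.2% (ICC 1%).

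**6. Fraction measured at which power falls to 80% (ICC 1-15%).**

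| Design | Pregnancy 24% vs 19.4% | Use 55% vs 62% |
|---|---|---|
| Nepal/Sri Lanka, of 32,400 | 30-34% | 18-21% |
| Tanzania, equivalent of 21,600 | 40-44% | 24-27% |

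For pregnancy, Nepal would cross its threshold only if fewer than about 0.30/0.44 = 68% to 0.34/0.44 = 77% of women lived within 24 hours.

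**7. Illustration on assumed fractions (not in the article).** If 30% or 20% of Sri Lankan enrolees were measured, pregnancy power would be about 75-80% or 58-63%. For a Tanzanian clinic sample equal to 30% or 20% of 21,600 it would be about 64-69% or 48-51%.

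**The case against.** The strongest reply is that no stated power claim is shown to fail. Nepal is the only country whose followed fraction can be bounded from the text, and it clears 80% at its ceiling. Every figure below 80% in step 7 rests on fractions that I assumed. Clinics are chosen partly by the percentage of delivering women who may attend them, so the true shares could be large. All of this stands. A reader might infer that the trial is underpowered at 18 months. The documents do not support that.

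Three further limits also stand:

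- The counts of 972 and 1,836 are not ceilings. The plan treats 8% uptake as a detectable rate and allows for more.
- The 6-week reference may be a stale label and not an orphaned endpoint, since the article describes use only at 9 and 18 months. The full outcome list (Additional file 1) is not shown, so one cannot conclude that a planned endpoint lacks data. Nor is the absence of a separate 9-month power statement an error in itself, because a condensed article may leave it to the full protocol.
- Tanzania's follow-up sample is recruited separately, so a share of enrolled women multiplied by 0.80 does not describe it. Its thresholds are only equivalents in numbers of women.

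What the reply does not remove is that the text powers a contrast its surveys cannot supply and uses an 18-month denominator that its eligibility rules exclude. Home visits and telephone contact reduce loss among selected women; they do not widen selection.

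**Conclusion.** The concern holds as an inconsistency between the power section and the follow-up plan. The 6-week contraceptive-use contrast cannot be estimated as stated. The 18-month statements rest on the wrong population (antenatal enrolees) and on too large a denominator. The excess is quantified only for Nepal: 25,920 assumed against at most 14,256. For Sri Lanka and Tanzania it is unknown.

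Under the model above, Nepal at its ceiling keeps about 89-93% power for pregnancy and 98-99% for contraceptive use. A fall below 80% needs the measured numbers to drop under the thresholds in step 6, which is possible but not shown.

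These figures assume two-sided 5%, ICC 1-15% and hospital effects that do not change over time, which is favourable. With an assumed cluster autocorrelation of 0.99 and ICC 15%, pregnancy power in the Nepal/Sri Lanka design is about 68% at 80% measured and 59% at 44%. The margin reported here should therefore not be read as the plan's own.

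**What to change.** 1. Replace the 6-week contraceptive-use power statement with one for the measured time points, 9 and 18 months. Keep the 55% and 62% rates or justify new ones for those times, since the 18-month statement borrows them.
2. Restate 18-month power for contraceptive use and pregnancy per country on the number expected to be followed: Nepal, 0.55 x share within 24 hours x 0.80; Sri Lanka, catchment share x 0.80; Tanzania, the expected number of clinic-recruited interviews.
3. Qualify the closing sentence on excellent power accordingly.
4. Change the two references to antenatal enrolment to enrolment after delivery.

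The cost is restated figures that are somewhat less favourable. Design, data collection and analysis do not change.

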### Data collection procedures

#### Quantitative

All quantitative data will be collected by trained interviewers using an electronic Computer-Assisted Personal Interview (CAPI) format using the Dimagi CommCare survey management system on Android-based tablets. At baseline, women will be approached by study interviewers in postnatal wards and asked if they are interested in learning about the study. Women who are interested in learning more are provided with an informed consent form (Additional file 2) that is read aloud by the study interviewer. Women who consent to participate will sign or provide a thumbprint. The signature is captured electronically on the tablet, but women will be given the option to sign the paper copy if they prefer not to sign electronically. Tablets are used to take a photo of paper copies of signatures or thumbprints so that provision of consent is fully electronic. Baseline interviews collect information on the extent of counseling the woman received and to assess the primary outcome, PPIUD uptake. At the time of the baseline interview, women will be asked to provide their contact information, including their phone numbers as well as those of friends and family and directions to their homes to facilitate contact for follow-up interviews.

At the end of the baseline interview, women who have accepted PPIUD will be asked to return to the facility for a PPIUD check-up 4–6 weeks after delivery. Data collectors will complete the 4-6 week survey when participants return to the health facility for this check-up. The 9-month and 18-month surveys are based on the Demographic and Health Surveys (DHS) questionnaire format and will be conducted when women return to the health facility for their child’s vaccinations. Women who do not return to the health facility as scheduled will be called and asked to come to the facility for their interview. Women’s travel costs to the health facility will be reimbursed by the study. In the event that women are unable to return, interviewers may attempt to interview them at their homes or another convenient location. Data quality will be ensured through phone re-interviews of approximately 5% of study participants, conducted by the interview supervisor.

Providers selected for the baseline survey will be interviewed using the CommCare survey management system 6 months after the intervention begins, and 12 months after the intervention ends by trained interviewers. In the follow-up surveys, all providers who completed the baseline interview will be selected, including those who have left the facility, in order to capture the extent to which diffusion has occurred. At 12 months after the end of the intervention, new staff at the study hospitals, who arrived after the intervention period was completed, will also be sampled to evaluate the extent to which PPIUD has been institutionalized. Extensive follow-up information is collected on each provider’s contact information as well as information of a friend or family member to aid in retention.

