#### Providers

The provider sample includes all medical personnel who could potentially provide PPIUD who are working in the study hospitals during the 15-month intervention period, along with those who are working in the hospitals 12 months after the end of the study period. In Sri Lanka, only doctors are eligible to provide PPIUD services, and all eligible doctors were included. In Nepal and Tanzania, a random sample of providers was selected to participate in the Provider Survey. A full list of doctors and nurses eligible to provide PPIUD services was obtained, and stratified random sampling was used to select an equal number of providers from each cadre in each facility to complete the survey.

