#### Training of providers

The facilities chosen in each country are primarily teaching hospitals who wish to include PPIUD as part of the regular OB/GYN training program and to integrate it as part of the standard delivery practice in these institutions. Health professionals will be trained through a combination of specific classroom-based training sessions and on the job training and mentoring, with new staff undertaking training as they rotate to the facilities.

Courses for approximately 12 master trainers, two from each participating hospital, will be organized. The training will include lectures, videos, web-based learning material, master classes and practical exercises on mannequins. Supervised IUD insertions and counselling sessions on patients will subsequently take place in order to establish competency.

These master trainers, who will be respected health care professionals with experience in implementing evidence-based clinical practices, will subsequently train the resident obstetrician/gynaecologists, the health facilities’ delivery team, the facilities’ antenatal team, and the community midwives in PPIUD related service delivery. All health providers involved in the project will be trained on counselling women on the benefits of adopting a postpartum contraceptive method for birth-spacing and maternal and infant health.

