### Outcome measures

Study outcomes will be assessed using a variety of research instruments. Quantitative interviewer-administered surveys will be conducted with women at up to four time points:Baseline (in hospital after delivery)4–8 weeks after delivery among women who accepted PPIUDProviders ask women to get a PPIUD check-up at 4-6 weeks postpartum, and these data can be collected between 2-12 weeks after delivery
9 months after deliveryCan be collected 8-14 months after delivery
18 months after deliveryCan be collected 15-21 months after delivery

Quantitative interviewer-administered surveys will also be conducted with providers at three time points:Baseline, prior to implementation of FIGO intervention6 months after implementation begins12 months after implementation ends

A facility survey using a checklist will also be completed before the intervention, 6 months after the intervention has begun, and 12 months after the end of intervention implementation to examine the extent to which PPIUD counselling and services have been institutionalized.

Primary and secondary outcomes are listed in Additional file 1, and key outcomes of interest are described in greater detail below:Uptake of PPIUDTo ascertain what percentage of women delivering in study hospitals take up PPIUD, participants will be interviewed after delivery, before they are discharged from the hospital
Receipt of PPIUD counseling before or after deliveryTo ascertain what percentage of women delivering in study hospitals receive counseling on PPIUD, participants will be interviewed after delivery, before they are discharged from the hospital. They will also be asked questions to assess the quality of the counseling.
PPIUD expulsion rate and complication rate at 4-8 weeks postpartumParticipants who have not deliberately removed the PPIUD will be examined by providers at 4-8 weeks postpartum, and providers will report whether the PPIUD was expelled or complications occurred.
Modern contraceptive use at 9 months postpartumParticipants will be interviewed at 9 months and asked whether they are using a modern method of contraception, defined as pill, implant, injectable, IUD, condom, or sterilization for the purposes of this study.
Modern contraceptive use at 18 months postpartumParticipants will be interviewed at 18 months and asked whether they are using a modern method of contraception.

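### The protocol contradicts itself on which providers are surveyed 12 months after implementation, and one frame omits staff who join during the intervention

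*Protocol article*

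**What the plan says.** Four places in the protocol article bear on who is surveyed.

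- **Data collection procedures, Quantitative.** At follow-up, "all providers who completed the baseline interview will be selected, including those who have left the facility". At 12 months after the end, a second group is added: "new staff at the study hospitals, who arrived after the intervention period was completed, will also be sampled".
- **Outcome measures.** The first provider survey is set at "Baseline, prior to implementation of FIGO intervention". Three sustainability percentages are then defined at 12 months after implementation ends: (1) trained providers still providing PPIUD; (2) trained providers who provide it in a new facility after transfer; (3) new providers, not originally trained, who provide it in the intervention facilities. None is limited to baseline completers or to staff who arrived after the intervention.
- **Training of providers.** Training is continuous, "with new staff undertaking training as they rotate to the facilities".
- **Participant selection criteria, Providers.** The sample is all personnel who could provide PPIUD and are "working in the study hospitals during the 15-month intervention period, along with those who are working in the hospitals 12 months after" the study period ends. I take this to be the same 12-month survey. The section then describes sampling in the past tense. For Nepal and Tanzania, "A full list of doctors and nurses eligible to provide PPIUD services was obtained" and a stratified random sample was drawn from it. In Sri Lanka all eligible doctors were included.

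**The concern.** A provider who arrives after the baseline survey but before the intervention ends cannot have completed a baseline interview and did not arrive after the intervention. Under the data collection section that provider is not interviewed. The protocol itself expects such people: the sites are mainly teaching hospitals, new staff are trained on arrival, and transfer is described as normal practice in all three countries.

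Institutionalization and diffusion are stated aims, and the provider survey is their main quantitative source. Staff who rotate in, are trained and move on are one route by which the service could spread. If they are not sampled, the percentages describe a narrower group than their labels say. Analysis cannot recover providers who were never interviewed. Because another section gives a wider frame, field teams working from different sections would interview different people.

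**Working it through.** The protocol gives no number of providers, number trained, staff turnover or precision target for these outcomes, so there is no stated figure to reproduce. The check is a comparison of frames, followed by an illustration on assumed values.

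**1. Frames against outcome populations**

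| Provider | Data collection section | Providers section | Outcome population |
|---|---|---|---|
| Baseline completer, trained | In, even after leaving | In | 1, and 2 if transferred |
| Joined during intervention, trained, still in post | Out | In | 1 or 3, depending on the meaning of originally trained |
| Joined during intervention, trained, since transferred | Out | In | 1 and 2 on the broad meaning; none on the narrow |
| Joined during intervention, not trained, still in post | Out | In | 3 |
| Arrived after intervention, in post at 12 months | In | In | 3 |

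On the broad meaning, originally trained covers anyone trained under the programme, and trained joiners belong in outcomes 1 and 2. On the narrow meaning it covers only the first cohort, and trained joiners still in post belong in outcome 3. The data collection section samples them for neither. So the gap remains on either meaning, except that on the narrow one transferred joiners belong to no outcome. In Nepal and Tanzania, staff present at baseline but not drawn are represented by the random sample and are not part of the gap.

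**2. Length of the missed window** (Randomization of hospitals: enrolment period minus standard-of-care period)

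| | Group 1 | Group 2 |
|---|---|---|
| Tanzania | 12 − 3 = 9 months | 12 − 9 = 3 months |
| Nepal, Sri Lanka | 18 − 3 = 15 months | 18 − 9 = 9 months |

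The 15 months in the Providers section therefore fits only Group 1 in Nepal and Sri Lanka.

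**3. Possible share of joiners.** Assume constant headcount and annual turnover r (not in the protocol). Over m months, the share of ever-eligible staff who joined during the intervention is (r·m/12) / (1 + r·m/12). For r = 25% and m = 9 this is 0.1875/1.1875 = 15.8%.

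| Assumed r | 3 months | 9 months | 15 months |
|---|---|---|---|
| 10% | 2.4% | 7.0% | 11.1% |
| 25% | 5.9% | 15.8% | 23.8% |
| 50% | 11.1% | 27.3% | 38.5% |

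**4. Possible error in a percentage.** Let f be the joiners' share of trained providers, and p_B and p_J the proportions still providing among baseline staff and joiners. The survey estimates p_B; the target is (1 − f)·p_B + f·p_J. The error is f·(p_B − p_J). The table uses round assumed values of f, which extend beyond the shares in step 3.

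| Assumed f | Gap 0 | Gap 10 points | Gap 20 points | Gap 30 points |
|---|---|---|---|---|
| 10% | 0 | 1.0 | 2.0 | 3.0 |
| 25% | 0 | 2.5 | 5.0 | 7.5 |
| 50% | 0 | 5.0 | 10.0 | 15.0 |

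The sign follows the sign of the gap, which is unknown.

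**The case against.** The strongest reply is that the Providers section already includes joiners: its first clause covers anyone working during the intervention, and its second covers anyone in post at 12 months, whatever the arrival date. This stands as far as it goes. A reader might infer from the data collection section alone that joiners are definitely excluded, and the documents do not support that. They support a contradiction. The Providers section does not resolve it, because its sampling steps describe a list already obtained and mention no refresh.

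A second reply is that the outcome denominators are sound as written. This also stands. It would be tempting to say that the percentages are computed on wrong denominators, but the weakness is that one version of the sampling frame does not cover them.

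Third, following baseline completers after they leave is a recognised cohort design, and it does measure diffusion among staff present at the start. That is correct, so diffusion is not left unmeasured. Only later arrivals are at issue.

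Fourth, this is a condensed article, and the outcome list is in an additional file that is not shown. Detail may well sit elsewhere. But the article states two different frames, which is a conflict rather than an omission.

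Finally, nothing shows that joiners behave differently from baseline staff. This is accepted: bias is possible, not demonstrated.

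**Conclusion.** The point holds as an internal contradiction and a gap in frame coverage. If the data collection section is followed as written, the three sustainability and diffusion percentages will not represent the populations they name. The size and direction of the error cannot be determined from the protocol. Under the assumed values it runs from 0 to 15 points, and it is zero if joiners behave like baseline staff. A reader might go on to conclude that retention or diffusion will be overstated or understated. The documents support neither, since they give no turnover and no comparison of the two groups. The potential gap is smallest in Tanzania Group 2, with a 3-month window, and largest in Group 1 in Nepal and Sri Lanka, with 15 months. PPIUD uptake, which comes from the women's baseline interview, is not affected.

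**What to change.** 1. Reconcile the Providers, Outcome measures and Data collection (Quantitative) sections so that they give one frame for the 12-month survey.
2. Define originally trained: anyone trained under the programme, or only the first cohort.
3. Keep the baseline cohort and its repeat interviews.
4. At 12 months, sample eligible providers in post who were not in the baseline survey, regardless of arrival date, and record when they arrived and whether and when they were trained. Dropping the arrival-date limit agrees with the Providers section and is inexpensive.
5. Where programme training records exist, add a sample of trained joiners who have since transferred, within the same interview total. The protocol mentions no such register, so this depends on what was kept. When groups sampled at different rates are combined, weight by their sampling fractions.
6. If steps 4 and 5 cannot be done, restrict the trained-provider outcomes to providers present at baseline and report them under that label.
7. State the intervention length by group and country in the Providers section, in agreement with Randomization of hospitals.

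The cost is slightly fewer interviews in each existing group if the total is held fixed, and some effort to trace transferred joiners, for whom no baseline contact details will have been collected. Replacing the baseline cohort wholly with a sample from training records is not recommended, because it would give up the repeat interviews.
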